### 5.2.3 Secondary efficacy analyses

Data regarding the secondary efficacy variables will be presented by treatment group and will be reported for the ITT and PP populations. Evaluations on the PP population would be considered as sensitivity analyses.

The statistical analysis of the single components of the composite endpoint will be conducted with the same approach adopted for the primary efficacy variable.

The other secondary efficacy variables will be analysed according to their type.

Discrete variables will be summarized by frequencies and percentages. Percentages will be calculated according to the total number of patients assigned to each interventional group and to the total number of patients included in the specific analysis population. The proportions of events occurred in the two interventional arms will be compared with the chi-square test for heterogeneity or the Fisher's exact test, if appropriate.

Continuous variables will be summarized by use of standard measures of central tendency and dispersion: mean, standard deviation (SD), standard error (SE), median, minimum, maximum, interquartile range (IQR). The average values of each parameter observed in the two interventional arms will be compared by means of the Wilcoxon two-sample test.

No adjustment for multiplicity will be adopted.

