### 150 **Sample Size Calculation**

151 The frequency of the composite primary outcome in the participating Italian neonatal units is about  
152 47% (severe IVH 8.0%, BPD 24.4%, mortality 14.6%). Meta-analyses showed a reduction of 32%  
153 in in-hospital mortality and of 17% in any IVH in preterm infants assisted at birth with delayed cord

154 clamping instead of immediate cord clamping (6;24). Moreover, no data on the incidence of  
155 outcomes between UCM and delayed cord clamping is available. Thus, we arbitrarily hypothesized  
156 that neonatal assistance with PCI might decrease the frequency of the composite primary outcome  
157 from 47% to 28%. Considering a dropout rate of 5%, we calculated that 106 newborns must be  
158 enrolled in each group to detect this difference as statistically significant with 80% power at a level  
159 of 0.05 using a 2-sided chi-square test.

160

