## 2.7 SAMPLE SIZE

Assuming a proportion of events (grade 3 or 4 IVH, moderate or severe BPD or death from any cause) equal to 47% in the control arm and equal or less than 28% in the experimental arm, corresponding to a relative reduction of the unfavourable events equal to 40%, it was calculated that a sample size of 200 preterm infants (100 per group) would have guaranteed a study power equal to 80%, with a two-sided alpha error equal to 5%, for a standard chi-square test for heterogeneity.

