#### 4.1.2 Secondary efficacy variables

The secondary efficacy variables are:

- The single components of the composite endpoint
- The variables reported in list below:
  - 1 min Apgar score
  - 5 mins Apgar score
  - FiO2 max in delivery room
  - Use of neopuff
  - Use of physiological solution
  - Use of sodium bicarbonate
  - Body temperature (°C) at intensive care admission
  - Surgical treatment for patent ductus arteriosus (PDA)
  - Incidence of IVH
  - Use of non-invasive mechanical ventilation
  - Duration of non-invasive mechanical ventilation (days)
  - Use of invasive mechanical ventilation
  - Duration of invasive mechanical ventilation (days)
  - iNO administration
  - Duration of iNO administration (days)
  - Need of erythrocyte concentrate transfusions
  - Number of erythrocytes concentrate transfusions
  - Use of oxygen therapy
  - Duration of oxygen therapy (days)
  - FiO2 max during oxygen therapy (%)
  - Dopamine use in the first 24 hours
  - Dobutamine use in the first 24 hours
  - Overall duration of hospitalization (days)
  - 3-hour cerebral oxygenation
  - 6-hour cerebral oxygenation
  - 12-hour cerebral oxygenation
  - 18-hour cerebral oxygenation
  - 24-hour cerebral oxygenation
  - Superior vena cava blood flow in the first 24 hours (ml/Kg/min)
  - PAP value (mmHg)
  - Right ventricular ejection (ml/Kg/min)
  - Left ventricular ejection (ml/Kg/min)
  - Presence of transductal shunt
  - Hb max (g/dl) in the first 24 hours
  - Ht max (%) in the first 24 hours
  - 3-hour average PAS (mmHg)
  - 6-hour average PAS (mmHg)
  - 12-hour average PAS (mmHg)
  - 18-hour average PAS (mmHg)
  - 24-hour average PAS (mmHg)

S/D AMS  
PI AMS  
RI AMS  
AMS diastolic flow  
S/D ACA  
PI ACA  
RI ACA  
ACA diastolic flow

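### Hospital stay, support durations and BPD alone are analysed over all randomised infants with no rule for deaths, so unequal mortality between arms distorts them

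*Combined protocol and SAP*

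**What the plan says.** SAP section 3 puts the secondary efficacy analyses on the intention-to-treat population, which section 3.2 defines as all randomised infants. Infants who die are therefore included.

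SAP 4.1.2 lists as efficacy variables the durations of non-invasive ventilation, iNO and oxygen, as well as "Duration of invasive mechanical ventilation (days" and "Overall duration of hospitalization (days", all counted in days. For continuous variables SAP 5.2.3 states: "The average values of each parameter observed in the two interventional arms will be compared by means of the Wilcoxon two-sample test".

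For BPD alone, SAP 5.2.3 states: "The statistical analysis of the single components of the composite endpoint will be conducted with the same approach adopted for the primary efficacy variable". Under SAP 5.2.2 that means percentages over all infants assigned, a chi-square or Fisher test, and a logistic odds ratio. Table 4.6 has rows for No, Yes and Missing value. It has no row for death before 36 weeks.

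The only related rule is SAP 4.3, which shows missing values as their own category and does not mention death. SAP 5.2.3 applies no multiplicity adjustment. The protocol's Sample Size Calculation gives local component rates of "severe IVH 8.0%, BPD 24.4%, mortality 14.6" per cent.

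**The concern.** A hospital stay or a period of support ends at death. An infant who dies in the first days therefore has a short stay, and the Wilcoxon test treats a short stay as a good one. BPD is assessed at 36 weeks, so an infant who died earlier cannot have it diagnosed. That infant still counts in the denominator of the BPD percentage, whether recorded as No or as Missing value.

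BPD and the duration of respiratory support are secondary outcomes in the protocol. SAP 2.2 hypothesises that assistance with intact placental circulation lowers mortality. If it does, that arm would tend to show a longer stay and a higher BPD percentage because more of its infants lived. A reader could then see secondary results that contradict the primary for a purely mechanical reason.

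**Working it through.** **Arm size.** The plan's own figure is checked first. For 47% against 28%, two-sided 5%, 80% power and pooled variance:

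n = [1.960·√(2·0.375·0.625) + 0.842·√(0.47·0.53 + 0.28·0.72)]² / 0.19² = 1.907² / 0.0361 = 100.7, or 101 per arm.

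At 100 per arm the power is 79.7%. Dropout of 5% gives 100/0.95 = 105.3, or 106. The SAP's 100 and the protocol's 106 therefore reproduce and are not in dispute. The documents give no figure for the durations or for BPD alone.

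**Expected deaths.** 0.146 × 200 = 29.2 and 0.146 × 212 = 31.0, so about 15 per arm.

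**BPD alone.** Assume the 24.4% is over all infants and every BPD case is alive at 36 weeks. The rate among survivors is r = 24.4/85.4 = 28.6%. Over all assigned infants it is r(1 − m), where m is mortality. The protocol's 32% reduction gives 14.6 × 0.68 = 9.9%. It comes from delayed against immediate clamping, so it is only an illustration here.

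**Durations.** Suppose survivors are identical in both arms and every death has a shorter duration than every survivor. The probability that an infant in the higher-mortality arm has the longer duration is P = 0.5 − (m_high − m_low)/2. The standard error is √[(n₁+n₂+1)/(12·n₁·n₂)], which at 100 per arm is √(201/120,000) = 0.0409. This gives an approximate upper bound on rejection.

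The last column simulates hospital stay (3,000 runs, 100 per arm). Its medians are assumptions, not document figures: 65 days for survivors and 8 days for deaths. No scenario has any treatment effect in survivors. The BPD rejection column assumes deaths are coded No.

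| Mortality, higher v lower | BPD, all assigned | Odds ratio | BPD rejection | P (bound) | Duration rejection, at most | Simulated stay |
|---|---|---|---|---|---|---|
| 14.6% v 14.6% | 24.4% v 24.4% | 1.00 | 5.0% | 0.500 | 5.0% | 4.8% |
| 14.6% v 9.9% | 24.4% v 25.7% | 0.93 | 5.5% | 0.477 | 8.8% | 8.2% |
| 20% v 10% | 22.9% v 25.7% | 0.86 | 7.6% | 0.450 | 23% | 20.6% |
| 25% v 5% | 21.4% v 27.1% | 0.73 | 16% | 0.400 | 69% | 64% |

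BPD among infants alive at 36 weeks is 28.6% in both arms in every row.

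**Mortality doubled in one arm (29.2% v 14.6%), 106 per arm.** The shift in P is 0.146/2 = 0.073 and the standard error is √(213/(12·106²)) = 0.0397. Then z = 1.84 and rejection is at most about 45%. BPD over all assigned is 28.6% × 0.708 = 20.2% in the higher-mortality arm.

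**Direction for invasive ventilation.** This was simulated for the three unequal-mortality rows, again with assumed distributions.
- Users only, with deaths shorter (median 3 against 6 days): P = 0.490, 0.481, 0.462. The higher-mortality arm looks better.
- Half of survivors scored 0 days and all deaths ventilated: P = 0.512, 0.525, 0.551. The higher-mortality arm looks worse.

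The sign depends on a rule that the SAP does not give.

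**The case against.** The strongest reply is that death is not ignored. The primary endpoint combines BPD with death, and Table 3.1 cross-tabulates IVH, BPD and death by arm. Both BPD or death and BPD among survivors can be worked out from that table. Mortality is also tested separately in Table 4.11. If mortality doubled in one arm, that test would be significant about 73% of the time at 106 per arm, so a reader would usually see the deaths. This stands as far as it goes. However, Table 3.1 is descriptive, and nothing in it corrects the test on BPD alone or on any duration.

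A second reply is that SAP 4.3 may place deaths under Missing value. If the BPD test then uses only No and Yes, it is in effect a test on survivors. That is possible, but the SAP does not say so. The percentage, taken over all assigned, would still be diluted and would no longer match the test beside it.

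Third, a reader might infer that every listed duration favours the arm with more deaths. The documents do not support that. It holds for hospital stay when deaths come before survivors' discharge, and for oxygen days if deaths are early. For invasive ventilation and iNO it can reverse if never-users score 0.

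Fourth, a reader might take 45% as the expected chance of a false finding. It is an upper bound under a doubling of mortality that nothing in the documents suggests.

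**Conclusion.** The omission is real and goes beyond missing detail. Applied as written to all randomised infants, the Wilcoxon test on hospital stay and the BPD percentage mislead whenever mortality differs between arms.

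The size depends on the mortality gap. There is no distortion at equal mortality. At the cited 32% reduction it is 1.3 percentage points on BPD and at most about 9% rejection for durations. Larger figures belong to assumed scenarios.

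The BPD figures assume that all BPD cases survive to 36 weeks. The protocol's own sum (8.0 + 24.4 + 14.6 = 47.0) treats the components as non-overlapping, which is consistent with that assumption, but it gives no denominators. The duration bound assumes that every death ranks below every survivor.

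A reader might also infer that the primary result is at risk. It is not, because death is part of the composite. The point concerns secondary outcomes and should be settled before database lock.

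**What to change.** In SAP 4.1.2 and 5.2.3:

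- **Durations.** Keep the Wilcoxon test, but rank death before discharge (or before 36 weeks) as the worst value for each duration. State which cut-off applies. Score surviving never-users as 0 days. Show raw durations in survivors descriptively, without a test.
- **Alternative.** Days alive and free of the support may be used instead if the horizon is a fixed number of days from birth. Thirty-six weeks is not such a horizon: it falls 91 days after birth at 23+0 weeks and 43 days at 29+6. The necessary dates must also be available. The protocol says that durations are collected but does not list start, stop or death dates among the recorded data.
- **BPD alone.** Base both the percentage and the test on infants alive at 36 weeks, labelled as conditional on survival. Report BPD or death by 36 weeks beside it. Under the assumptions above that would be 24.4 + 14.6 = 39.0% at 14.6% mortality and 25.7 + 9.9 = 35.7% (before rounding of the parts) at 9.9%, so it moves in the same direction as mortality.

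The cost is a short SAP paragraph, some extra derivation and slightly less familiar summaries. With death ranked worst, each duration test also responds to mortality, so it should be labelled as a combined measure. BPD among survivors is not a fully randomised comparison, which is why the combined figure belongs next to it.

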### 5.2.4 Safety Analyses

Data regarding the safety variables will be presented by treatment group and will be reported for the safety and PP populations. Evaluations on the PP population would be considered as sensitivity analyses.

The statistical analysis of the safety parameters will be conducted with the same approach adopted for the other secondary efficacy variable.

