### 305 **Statistical Analysis**

306

307 The primary efficacy analysis will be conducted on an intention-to-treat basis and the per-  
308 protocol approach for a secondary sensibility analysis. Clinical characteristics of infants in PCI  
309 and UCM groups will be described using mean values and standard deviation, median value and  
310 range, or frequencies and percentage.

311 Univariate statistical analysis will be performed using the Wilcoxon rank-sum test for continuous  
312 variables and the chi-square test or Fisher's exact test when appropriate for categorical variables.

313 A two-sided P value <0.05 will be considered statistically significant.

314 Relative effect estimates will be expressed as odds ratio (OR) with Wald 95% confidence limits.

315 With explorative intent we will evaluate the heterogeneity of the results within the two groups of  
316 newborns stratified by the type of delivery.

317 Statistical analysis will be performed with SAS System version 9.4 (SAS Institute Inc.).

318

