### 2.3.2 Secondary objectives

- To compare in the two groups of preterm infants in which assistance with intact placental circulation or assistance after cord milking has been given the proportion of subjects experiencing at 36 weeks of post-conceptual age each of the events included in the composite outcome.
- To assess the presence of interaction between type of assistance and gestational age, and between type of assistance and type of delivery, on the primary composite endpoint and on each of its components.
- To compare in the two groups of preterm infants in which assistance with intact placental circulation or assistance after cord milking has been given the results related to the identified secondary efficacy endpoints.
- To evaluate the safety of the two assistance strategies.

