## **APPENDIX 1 - PLANNED DATA DISPLAY**

**NOTE**

- (1) Chi-square tests, measures based on chi-square and Fisher's exact test are reported below the primary table.
- (2) The proportions of events observed in each arm, their 95% exact confidence intervals, the difference between the two proportions and its exact confidence interval are reported below the primary table.
- (3) The standard output of the logistic regression model is reported below the primary table.
- (4) The standard output of the logistic regression model including the interaction term between interventional arm and stratification factor is reported below the primary table.
- (5) The standard output of the Wilcoxon rank-sum test is reported below the primary table.

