|                                | Arm A         |   | Arm B |   |       |   |
|                                | N             | % | N     | % | N     | % |
| Pharmacological closure of PDA |               |   |       |   |       |   |
| No                             |               |   |       |   |       |   |
| Yes                            |               |   |       |   |       |   |
| Missing value                  |               |   |       |   |       |   |
| Total                          |               |   |       |   |       |   |

NOTE: Arm A = UMBELICAL CORD MILKING, Arm B = DELAYED UMBELICAL CORD CLAMPING

TABLE 6.13: DISTRIBUTION OF PATIENTS BY NECROTIZING ENTEROCOLITIS AND TREATMENT ARM (1)

*SAFETY POPULATION*

|               | Treatment Arm |   |       |   | Total |   |
|---------------|---------------|---|-------|---|-------|---|
|               | Arm A         |   | Arm B |   |       |   |
|               | N             | % | N     | % | N     | % |
| NEC           |               |   |       |   |       |   |
| No            |               |   |       |   |       |   |
| Yes           |               |   |       |   |       |   |
| Missing value |               |   |       |   |       |   |
| Total         |               |   |       |   |       |   |

NOTE: Arm A = UMBELICAL CORD MILKING, Arm B = DELAYED UMBELICAL CORD CLAMPING

TABLE 6.14: DISTRIBUTION OF PATIENTS BY PERIVENTRICULAR LEUKOMALACIA AND TREATMENT ARM (1)

*SAFETY POPULATION*

|               | Treatment Arm |   |       |   | Total |   |
|---------------|---------------|---|-------|---|-------|---|
|               | Arm A         |   | Arm B |   |       |   |
|               | N             | % | N     | % | N     | % |
| PLV           |               |   |       |   |       |   |
| No            |               |   |       |   |       |   |
| Yes           |               |   |       |   |       |   |
| Missing value |               |   |       |   |       |   |
| Total         |               |   |       |   |       |   |

NOTE: Arm A = UMBELICAL CORD MILKING, Arm B = DELAYED UMBELICAL CORD CLAMPING

TABLE 6.15: DISTRIBUTION OF PATIENTS BY INTRAVENTRICULAR HEMORRHAGE AND TREATMENT ARM (1)

*SAFETY POPULATION*

|               | Treatment Arm |   |       |   | Total |   |
|---------------|---------------|---|-------|---|-------|---|
|               | Arm A         |   | Arm B |   |       |   |
|               | N             | % | N     | % | N     | % |

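### SAP 5.2.4 gives the safety variables a between-arm p-value but no between-arm estimate or confidence interval, so a non-significant result would not show how much harm remains possible

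*Combined protocol and SAP*

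**What the plan says.** SAP 2.3.2 lists among its objectives "To evaluate the safety of the two assistance strategies". SAP 5.2.4 gives the method: "The statistical analysis of the safety parameters will be conducted with the same approach adopted for the other secondary efficacy variable".

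That sends the reader to SAP 5.2.3. For categorical variables, "Discrete variables will be summarized by frequencies and percentages", and the two arms' proportions "will be compared with the chi-square test for heterogeneity or the Fisher's exact test, if appropriate". Continuous variables get summary statistics by arm and "will be compared by means of the Wilcoxon two-sample test". The threshold is in the protocol's Statistical Analysis section: "A two-sided P value <0.05 will be considered statistically significant".

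Appendix 1 of the SAP shows the planned output. Every categorical safety table (6.1-6.5, 6.9, 6.10, 6.12-6.17) carries note (1) only: chi-square tests, chi-square-based association measures and Fisher's test. Every continuous one (6.6-6.8, 6.11) carries note (5) only, the Wilcoxon output. Note (2) provides per-arm exact intervals and adds that "the difference between the two proportions and its exact confidence interval are reported below the primary table". It is attached to tables for the composite and its components, never to a Section 6 table. The same is true of note (3), the logistic model.

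The protocol's Statistical Analysis section also has a general rule, not limited to any endpoint, that relative effects are given as odds ratios with Wald 95% limits. SAP 5.2.3 and 5.2.4 do not carry that rule over to the safety variables.

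**The concern.** A p-value above 0.05 does not say how large an excess of harm the data still allow; an interval does. The trial was sized for a 19-point difference in a composite expected in 47% of controls. Many safety variables (NEC, PVL, chest compressions, adrenaline in the delivery room) may be much rarer than that. For a rare event, a non-significant result is the likely outcome even if the risk has doubled. A report that follows the plan literally would show two percentages and a p-value. A reader could take that as evidence that assistance with an intact cord is as safe as milking, when the data had not excluded a clinically important increase.

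**Working it through.** **1. Which outcomes lack an interval.**

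| Outcome | Table | Notes attached | Between-arm estimate and CI planned? |
|---|---|---|---|
| Grade 3-4 IVH (ITT) | 4.1 | 1, 2, 3 | Yes |
| Moderate/severe BPD (ITT) | 4.6 | 1, 2, 3 | Yes |
| Death (ITT) | 4.11 | 1, 2, 3 | Yes |
| Categorical safety variables | 6.1-6.5, 6.9, 6.10, 6.12-6.17 | 1 | No |
| Continuous safety variables | 6.6-6.8, 6.11 | 5 | No |

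**2. Reproducing the plan's sample size.** Inputs from SAP 2.7: 47% v 28%, two-sided 5%, 80% power, chi-square test. With pooled variance,

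n = [1.960·√(2·p̄·q̄) + 0.8416·√(p1q1 + p2q2)]² / (p1 − p2)²

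where p̄ = 0.375. So n = [1.960 × √0.46875 + 0.8416 × √0.4507]² / 0.19² = (1.342 + 0.565)² / 0.0361 = 100.7, that is 101 per arm. The SAP states 100, at which power is 79.7%. With 5% dropout, 101/0.95 = 106.3; the protocol states 106. The plan's figures reproduce.

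**3. Chance of detecting a doubling at the same size.** The normal approximation is

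power = Φ{[d·√n − 1.960·√(2·p̄·q̄)] / √(p1q1 + p2q2)}

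For 5% → 10% with n = 100: [0.05 × 10 − 1.960 × √0.13875] / √0.1375 = (0.500 − 0.730)/0.371 = −0.62, so power is 27%.

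For 10% → 20%: [1.000 − 1.960 × √0.255] / √0.25 = (1.000 − 0.990)/0.5 = 0.02, so power is 51%.

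Exact enumeration over two binomials, 100 per arm, two-sided 0.05. The SAP says only that Fisher's test is used where appropriate; the third column assumes this means an expected count below 5. All baselines are assumed.

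| True rates | Normal approx. | Chi-square, or Fisher if expected < 5 | Missed | Power with Fisher throughout |
|---|---|---|---|---|
| 3% → 6% | 17% | 12% | 88% | 9% |
| 5% → 10% | 27% | 27% | 73% | 19% |
| 10% → 20% | 51% | 52% | 48% | 44% |
| 12% → 24% | 60% | 61% | 39% | 54% |
| 20% → 40% | 88% | 88% | 12% | 84% |

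By the normal approximation, power passes 50% at a baseline of about 9.8% with 100 per arm and 9.3% with 106. At 106 per arm it is 28% from 5% and 53% from 10%, so the choice between the two stated sample sizes changes little. The safety population excludes infants assisted off protocol (SAP 3.4, 3.5), so its total cannot exceed the number randomized.

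**4. What an interval would add.** Suppose 5/100 v 10/100. Chi-square p = 0.18 (Fisher 0.28). The risk difference is +5.0 points with standard error √(0.05 × 0.95/100 + 0.10 × 0.90/100) = 0.0371. The simple Wald 95% interval is 5.0 ± 1.96 × 3.71, or −2.3 to +12.3 points; the odds ratio is 2.11 (0.69 to 6.42). The exact interval of note (2) will differ somewhat. The p-value alone reads as no difference, while the interval shows that an excess of about 12 points is not excluded.

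**The case against.** The other side has several good points.

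- *A reader might infer that safety rests on p-values alone.* It does not. Every binary safety table prints numbers and percentages by arm, note (1) adds chi-square-based measures, and anyone can compute a risk difference and interval from the counts. This makes the gap one of analysis and presentation, with no data lost. It remains a gap: the plan neither specifies the interval nor says how the safety results will be interpreted, and chi-square-based measures do not express an excess of events.
- *A reader might infer that the gravest harms have no interval.* Severe IVH, BPD and death do have one, as components of the composite. The protocol's component rates (8.0%, 24.4%, 14.6%) therefore cannot be used to show the size of the problem for the uncovered variables.
- *A reader might infer that a doubling would usually be missed whatever the outcome.* That holds only below a baseline of about 10%. At 20% it would be missed about 12% of the time. The documents give no rates for NEC, PVL, compressions or adrenaline, so where each falls is an assumption.
- *The protocol already has an odds-ratio rule.* It does, and the SAP does not revoke it. But SAP 5.2.4 and the table shells, which determine what is produced, do not apply it to safety. The two documents need to agree.
- *No passage says that non-significance will be reported as equal safety.* Correct. The documents plan no equivalence or non-inferiority claim, and the protocol's monitoring section adds review of serious adverse events for severity and causality. The risk is a misreading that the planned output does nothing to prevent.
- *An interval does not raise power.* Also correct: the same infants are analysed. The interval makes the imprecision visible.

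**Conclusion.** The point holds in a limited form. For the SAP 4.2 safety variables, the only planned between-arm inference is a p-value, shown beside descriptive results by arm. The protocol's general rule on odds ratios with confidence limits is not carried through. For complications with a baseline below about 10%, a true doubling would be non-significant more often than not at about 100 per arm: missed about 88% of the time from 3% and 73% from 5%, and close to even (48%) from 10%. These figures assume the stated baselines, equal arms, two-sided 0.05, and Fisher's test when expected counts are below 5; Fisher throughout would miss more.

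The primary analysis and the intention-to-treat results for severe IVH, BPD and death are untouched. The documents do not support a claim that the plan intends to declare equal safety.

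**What to change.** In SAP 5.2.4 and Appendix 1:

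- Attach existing note (2), the risk difference with its exact 95% confidence interval, to Tables 6.1-6.5, 6.9, 6.10, 6.12-6.14 and 6.16.
- Do the same for dichotomised versions of Table 6.15 (any IVH; grade 3-4 IVH) and Table 6.17 (any sepsis).
- Add one sentence stating that p > 0.05 will not be reported as evidence of equal safety.
- Say how the protocol's odds-ratio rule applies to these variables, so that the two documents agree.

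A Hodges-Lehmann difference with interval for the continuous variables is optional; it may say little for heavily tied counts such as surfactant doses. A formal rule based on the upper confidence limit is also not needed, and would be no decision rule without a margin, which the plan does not have.

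The cost is SAP wording and one more output line per table, using output already specified for the primary outcome. No extra infants or data are required. The price is a more cautious safety conclusion.
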